Funding:

Funding is provided by NIH-NIAMS U19AR076737 (Overall PI: [name]; directors of Bio-Behavioral Core: [name] and [name]) under title: UCSF Core Center for Patient-centric Mechanistic Phenotyping in Chronic Low Back Pain (UCSF REACH)

Research Plan and Hypotheses:

This is an exploratory, mechanistic observational study with 30 patients undergoing 8-week pre-post assessment without a control group for proof-of-concept: can mindful interoceptive exposure possibly recover decreased interoceptive awareness AND dysfunctional central pain processing, thereby potentially reducing pain impact?

Hypotheses:

This is a proof-of-concept observational study without rigorous testing of hypotheses. Preliminary hypotheses are:

1) the new brief mindful interoceptive exposure task (MIET) is feasible and is acceptable to patients with chronic low back pain (cLBP) (Primary Outcome)

2) in cLBP patients with low interoceptive awareness (= below average scores on the Multidimensional Assessment of Interoceptive Awareness; MAIA), an 8-week mobile phone-based interoceptive exposure task can increase interoceptive awareness and recover dysfunctional central pain processing (assessed by quantitative sensory testing, QST; and fMRI connectivity) (Secondary Outcome)

3) exploratory hypothesis: Pain intensity (NRS) and pain interference (PROMIS-29) will improve from pre to post intervention.

4) exploratory hypothesis: Improvements in pain intensity and interference will be correlated with changes in MAIA scores, QST and fMRI connectivity.

Specific Aims:

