| \| 1) to determine whether a mobile phone-based 8-week behavioral program of a brief mindful interoceptive exposure task (MIET) is feasible and acceptable to patients with cLBP.  2) to determine whether MIET can increase below-average interoceptive awareness (as assessed by the MAIA) in patients with cLBP. We will offer the MIET to the participants in the cohort studies of the BACPAC REACH study (U19) living in the Bay Area, applicants of the Intensive Pain Rehabilitation Program at the VA, and other patients with cLBP, and validate it on self-report outcomes (pain intensity/ interference) *and* objectively (QST and fMRI**)**with 30 participants over 8 weeks, who fit a low interoceptive awareness phenotype.  3) To assess potential changes in chronic pain-related attitudes, believes and coping styles secondary to the intervention. In addition to psychological questionnaires, we will use qualitative exit interviews in 20 selected participants to explore phenomenological differences in patients' attention styles that may be associated with benefits for pain scores.  4) to assess whether potential changes in self-reported pain outcomes and/or objective QST measures are correlated with potential changes in interoceptive awareness (MAIA). All 30 participants will undergo pre-post assessment of pain intensity (NRS), pain interference (PROMIS-29), and QST.  5) to assess whether changes in self-reported interoceptive awareness (MAIA) are associated with changes in brain activity and connectivity. All 30 participants will undergo pre-post assessment of the MAIA and the fMRI Anticipation/Attention task. \| \| --- \| |
| --- | --- |

Design:

This is an uncontrolled, exploratory, mechanistic observational pilot study without control group for the validation of a behavioral task in individuals with chronic pain.

All subjects undergo:

1) questionnaire tests

2) psychophysical testing of cutaneous thermal sensitivity. Using previously validated procedures, we will examine each participant's sensitivity to temperature stimulation.

3) Functional Magnetic Resonance Imaging (fMRI) on the brain.

4) daily pain assessments by electronic momentary assessments (EMA) over 8 weeks

Background and Significance:

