**Screening, consent, baseline questionnaires:** Potential participants will be informed about the study and screened for preliminary eligibility by phone by a clinical research coordinator (CRC) at the UCSF Osher Center. The screening will include a verbal consent to be screened and follow a screening script. Once deemed preliminarily eligible, potential participants will receive a study brochure, the consent forms by mail (with postmarked return envelope) and an invitation to schedule a further discussion by zoom with either the CRC or the PI. Recruitment and screening will occur by phone or Zoom from the UCSF Osher Center.

After signing informed both consent forms (One overall UCSF consent; one QST and fMRI-specific VA consent), they will answer questionnaires on-line at home (Qualtrics). If final eligibility is confirmed according to questionnaire answers, eligible participants will be informed and will be scheduled for quantitative sensory testing (QST) and fMRI at the San Francisco Veterans Affairs Medical Center (SFVAMC; Visit 1). The part of the study conducted at the SFVAMC will include phone calls and will not include any communication or screening using Zoom.

Subjects will be asked to provide an email address on the Informed Consent form to receive the questionnaire online via Qualtrics, an online research survey software with a securely built platform, widely used by academic institutions. The participants will be provided a unique subject ID and password and will be sent an email containing the Qualtrics link or a paper survey as an alternative option to be used for accessing the questionnaires. The questionnaires will take **45 - 60 minutes**.

**Visit 1**: A SRA at the SFVAMC will conduct the QST and fMRI. This will take **2-4 hours**.

All procedures done in Visit 1 have previously been approved ([name]: #14-13833; 19-28942)

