3. Men and women aged 18-65 years old. We are not enrolling younger children as they are not part of the Intensive Pain Rehabilitation Therapy program. 65 is our upper limit for age due to changes in blood flow on the MRI.

4. Eligibility will be assessed using the following questions: “(1) How long has back pain been an ongoing problem for you? and (2) How often has low-back pain been an ongoing problem for you over the past 6 months?” A response of greater than three months to question 1, and a response of “at least half the days in the past 6 months” to question 2 would meet the cLBP eligibility criterion.

5. Ability to speak English. We do not have the capacity, given the resources available in this proposal, to translate all course material and conduct groups into another language. We have previously enrolled Hispanic participants into other studies who were fluent in English, and expect to do this in the proposed study.

6. Low level of interoceptive awareness and habitual distraction as coping mechanism with pain. This is defined as:

a) MAIA summary score below the population mean score of 3.41.  The value of 3.41 is the mean value of a sample of primary care patients at Kaiser Permanente in a prior study.

b) the MAIA Non-Distraction score is below 2.91 [possible range 0-5].  The value of 2.91 is the mean value plus standard deviation in the same sample.^4^

This eligibility criterion was chosen to test the hypothesis that the MIET task will be able to increase interoceptive awareness in patients with chronic low back pain with below average interoceptive awareness and preference for distracting themselves from their pain experience.

7. Owning a smart phone: the task is smart phone-based.

Under NIH definition, all individuals under the age of 21 are considered children. Eligible participants who are 18 years of age or older will be recruited for this study. Younger children will not be included in this study because a pediatric sample may require different intervention approaches.

Exclusion Criteria:

1. Unable to provide informed consent.

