After making initial contact with the subject and prior to enrollment, eligibility screening will be conducted by trained research staff. Due to the extensive nature of the eligibility screening, participants will be asked to give verbal consent (see section 10.7) before the screen is conducted. If a potential subject is interested in participating and provides verbal consent, he or she will be asked a series of eligibility questions. If he/she meets initial requirements for preliminary eligibility and is interested in participating, the potential participant will be invited and potentially scheduled for a zoom-based appointment with the study team at the UCSF Osher Center.

Eligibility will be determined after 2 steps: (1) Potential participants, which have heard or read about the study, will be screened by phone by the SRA. If passing eligibility criteria and after providing informed consent, (2) provisionally eligible potential participants will sign informed consent and then answer the MAIA online at home by Qualtrics. If their summary score is below the population mean score of 3.41 and the Non-Distraction score is below 2.91 [possible range 0-5], they are fully eligible and will be informed by phone and/or e-mail about their eligibility by the SRA. The value of 3.41 is the mean value of a sample of primary care patients at Kaiser Permanente in a prior study, and the value of 2.91 is the mean value plus standard deviation in the same sample.^10^ This eligibility criterion was chosen to test the hypothesis that the MIET task will be able to increase interoceptive awareness in patients with chronic low back pain with below average interoceptive awareness and preference for distracting themselves from their pain experience.

Potential participants enrolled in REACH have passed the same eligibility criteria applied to the Mind your Pain study except one: the below-average value of the MAIA summary and Non-Distraction scores. Once reached over the phone and after providing informed consent, these provisionally eligible potential participants will answer the MAIA online at home by Qualtrics or REDCap. They will be eligible with the same below-average scores defined above.

Initiation of Contact/Recruitment:

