All data collected for eligibility purposes is collected via VA RedCap or Qualtrics and will remain electronic throughout the course of the study. While this data will not be used for analysis, it will be preserved as it is used to contact potential future participants (upon their consent to do so). All retained data collected is behind the secure UCSF firewall.

Subject identifiers will be kept separately from the research data in locked cabinets and locked office at the UCSF Osher Center.

Risks and Benefits:

Data are password-protected and stored on secured UCSF PHI drive, only accessible on UCSF server. The computers will be checked regularly for proper and safe operation. Identifiable information is also stored as a hard copy in a locked office and locked file cabinet. Subjects will be carefully screened and subsequentially informed about the fact that the principal investigator will be available at all times during the experiment. Subjects are informed that they may end the test session at any time and that participation in this research is voluntary.

Subjects are told that all information obtained is completely confidential and that their medical treatment at UCSF or the VA will not be affected, whether or not they choose to participate in this study. Coded numbers are assigned to each file in the data base to ensure patient privacy. To minimize the risk that sensitive subject information may be disclosed, all subject information will be kept in locked cabinets or in databases with secured passwords.

Records and data will be rigorously protected. Examiners will be clinically trained and sensitive to signs of stress, anxiety, or fatigue so that testing will be immediately terminated should any subject experience signs of discomfort. Any incidental findings regarding subjects' health will be submitted to his/her physician at subjects' request.

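### The MAIA score that admits a participant is also the baseline for MAIA change, so with no control group the change estimate is biased upward by regression to the mean

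*Protocol*

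**What the plan says.** Research Plan and Hypotheses describes "30 patients undergoing 8-week pre-post assessment without a control group". Hypothesis 2, a secondary outcome, states that "an 8-week mobile phone-based interoceptive exposure task can increase interoceptive awareness". Aim 2 is "to determine whether MIET can increase below-average interoceptive awareness (as assessed by the MAIA) in patients with cLBP". Neither sets a minimum increase.

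Inclusion criterion 6 requires a "MAIA summary score below the population mean score of 3.41" and a Non-Distraction score below 2.91. Of the second cut-off it says: "The value of 2.91 is the mean value plus standard deviation in the same sample".

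On timing, Determination of Eligibility says that "provisionally eligible potential participants will sign informed consent and then answer the MAIA online at home by Qualtrics". Procedures (screening, consent, baseline questionnaires) likewise places the at-home questionnaires after consent, and sets the condition "If final eligibility is confirmed according to questionnaire answers" before Visit 1 is scheduled. The Repeat Questionnaires paragraph then gives the same instruments at 8 weeks, apart from demographics and social background, and calls the first set baseline. Questionnaire Instruments lists the MAIA (37 items) without limiting it to one time point.

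Statistical Design and Power makes Cohen's d with a 95% confidence interval the main summary and names no denominator. The Consent Process section says of data collected for eligibility: "While this data will not be used for analysis, it will be preserved".

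**The concern.** A score below a cut-off is low partly because the person's usual level is low and partly because of chance on the day. The chance part does not persist, so the group mean is expected to rise on the next measurement even if nothing has been done. A control group selected in the same way would show the same rise and allow it to be subtracted. This study has none.

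The MAIA is both the selection variable and the outcome of Aim 2, and any increase counts in favour of hypothesis 2. An unadjusted pre-post rise would mix the effect of MIET with the effect of selection, and the effect size carried forward to later research would be too large. A statistical analysis plan could report an adjustment, but it cannot supply a pre-training measurement that was never scheduled.

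**Working it through.** **Step 1: is it one measurement?** Determination of Eligibility and Procedures both put the questionnaire step after signed consent, at home, in Qualtrics and before Visit 1. Both let its answers decide final eligibility. REACH enrollees follow the same sequence (Qualtrics or REDCap). Visits 1, 2 and 3 include no MAIA. The next one is in the 8-week repeat set. So the admitting score is the pre-score.

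**Step 2: inputs.** From the protocol: the summary cut-off is the reference mean, the Non-Distraction cut-off is the reference mean plus one SD, there is a single arm, and 30 patients with 10% attrition leave 30 × 0.9 = 27. Not in the protocol, so assumed: bivariate normal scores with equal SD, retest correlation r over 8 weeks, the mean of the recruited population, and no true change. The protocol gives no figure for MAIA change to reproduce; its detectable d of 0.78 was set for pain impact and is not used here.

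**Step 3: formulas.** Let c be the cut-off in SD units above the recruited population's mean.

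- Expected rise with no effect = (1 − r) × φ(c)/Φ(c) SD.
- At c = 0, φ(0)/Φ(0) = 0.399/0.5 = 0.798, and the variance of the selected first score is 1 − 0.798² = 0.363.
- SD of change = √[(1 − r)² × 0.363 + (1 − r²)].
- Paired d = expected rise / SD of change.

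**Step 4: results at c = 0.**

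| r | Expected rise (SD) | SD of change | Paired d |
|---|---|---|---|
| 0.9 | 0.1 × 0.798 = 0.08 | √(0.004 + 0.190) = 0.440 | 0.18 |
| 0.8 | 0.2 × 0.798 = 0.16 | √(0.015 + 0.360) = 0.612 | 0.26 |
| 0.7 | 0.3 × 0.798 = 0.24 | √(0.033 + 0.510) = 0.737 | 0.32 |

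Simulation of 2 million pairs per setting agrees. As an illustration only, since the protocol specifies no test on the MAIA: with 27 completers, a two-sided 5% paired t test would show a significant rise in about 15%, 25% and 36% of studies, against 2.5% nominally in that direction.

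**Step 5: sensitivity to the recruited population's mean.**

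| Mean relative to cut-off | φ(c)/Φ(c) | Rise at r = 0.9 / 0.8 / 0.7 (SD) |
|---|---|---|
| 0.5 SD below | 0.509 | 0.05 / 0.10 / 0.15 |
| Equal | 0.798 | 0.08 / 0.16 / 0.24 |
| 0.5 SD above | 1.141 | 0.11 / 0.23 / 0.34 |

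The rise is positive throughout. Widening r to 0.5–0.9 gives 0.05 to 0.57 SD over the three means.

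**Step 6: the Non-Distraction cut-off.** At c = 1, r from 0.9 to 0.5 gives a rise of only 0.03 to 0.14 SD on that scale. The summary cut-off drives the bias.

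**Step 7: with a second pre-training MAIA as baseline.** The expected artefact becomes (correlation of screening with new baseline − correlation of screening with week 8) × 0.798 SD. It is zero if the two are equal. If they are 0.8 and 0.7 (assumed), it is 0.1 × 0.798 = 0.08 SD, against 0.24 SD for the single MAIA at r = 0.7.

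**The case against.** The strongest reply is about weight. The primary outcome is feasibility and acceptability, which this does not touch. The protocol calls the study proof-of-concept, without rigorous hypothesis testing. Hypothesis 2 also rests on QST and fMRI, which are not selection variables. The size of the bias depends on two quantities that the documents do not give. All of this stands and lowers the severity. It does not remove the bias, because an effect size is shifted whether or not it is tested.

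Several stronger readings are tempting, and the documents do not support them:

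- **Regression to the mean alone would produce the finding.** It gives an expected rise in that direction. In the central case above, most studies would not show a significant rise from it alone.
- **Cohen's d is further inflated by a truncated baseline SD.** Selection at the mean does cut the baseline SD to √0.363 = 0.60 of the population value. That matters only if the baseline SD is the denominator, and the protocol names none. The SD of change falls by only about 2% to 5% for r from 0.9 to 0.7.
- **Aims 4 and 5 are distorted.** A shift in the mean MAIA change does not itself alter its correlation with pain, QST or fMRI change. Measurement error mainly weakens such correlations, and does so with any baseline.
- **The protocol has no baseline MAIA, because eligibility data will not be analysed.** That sentence follows text on the phone screen, taken under verbal consent, whereas the MAIA is answered after signed consent. The wording is loose and needs clarifying, but it does not show that the baseline is missing.

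**Conclusion.** The point holds for the MAIA change in hypothesis 2 and Aim 2. One MAIA both selects and serves as baseline, there is no control group, and no other pre-training MAIA is scheduled, so the estimate is biased upward for any retest correlation below 1. Under normality, no true change and a recruited-population mean at the cut-off, the bias is 0.08 to 0.24 SD for r from 0.9 to 0.7. The true size could be smaller or larger, since neither the retest correlation nor the recruited population's mean is known. This should be fixed. It does not threaten the primary outcome.

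**What to change.** 1. Use the screening MAIA for eligibility only. Re-administer it online after eligibility is confirmed and before the Visit 2 training, and state that this second score is the baseline for MAIA change.
2. Report the change in raw points and as a d whose denominator is not the truncated screening SD, for example the SD of change. A reference-sample SD cannot be taken from the protocol: 3.41 is a mean, and no SD of the summary score is given.
3. If a second MAIA is not possible, report the observed change beside the expected regression-to-the-mean shift over a stated range of retest correlation and source-population mean, and do not attribute the unadjusted rise to MIET.
4. In the Consent Process section, clarify that the statement on eligibility data does not cover the baseline questionnaires.

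The cost is one short extra online questionnaire per participant, a few sentences, and probably a smaller MAIA effect. Some regression remains if the screening score correlates more strongly with the new baseline than with week 8.
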